## Abstract

**Background:**

Anti-tuberculosis therapy requires at least six-month treatment with continuous administration of combined antibiotics, including isoniazid, rifampicin, pyrazinamide, and ethambutol. The long-term exposure to antibiotics could cause consequent changes in gut microbiota, which may alter the gastrointestinal function and drug absorption in patients, thereby affect the outcome of treatment. The study aims to characterize the longitudinal changes of gut microbiota among tuberculosis (TB) patients under standardized first-line treatment and provide an understanding of the association between alterations in gut microbiota composition and unfavorable clinical outcomes.

**Methods:**

The study is a multicenter, observational prospective cohort study. Three study sites are purposively selected in the western (Sichuan Province) and eastern (Jiangsu Province and Shanghai) parts of China. Three-hundred patients with bacteriologically confirmed pulmonary TB are enrolled. All eligible patients should be investigated using structured questionnaires before treatment initiation; and be followed up during the treatment at Day-14, Month-2, Month-5, the end of treatment and the sixth month after ending therapy. Stool samples are to be collected at each visit, consisting of six stool samples from each patient. Additionally, 60 healthy volunteers from Sichuan province and Shanghai city will be recruited as healthy controls to form the baseline of patient gut microbiota in the Chinese population. The dynamic changes of gut microbiota in terms of alpha diversity, beta diversity, taxonomic composition are to be illustrated individually from the time at diagnosis until the sixth month after therapy is completed. Furthermore, the diversity and component of gut microbiota will be compared between the groups with and without unfavorable treatment outcome in terms of adverse effect and treatment failure.

**Discussion:**

Studies on the clinical manifestations, adverse reactions, and gut microbiota alterations will provide scientifically-sound evidence on the impact of gut microbiota alterations on TB treatment outcomes. The study is not only useful for guiding personalized TB treatment but also sheds light on the effects of continuous antibiotics administration on gut microbiota.

**Trial registration:**

Chinese Clinical Trial Registry, trial ID: ChiCTR1900023369, May 24, 2019. Retrospectively registered.

## Background

Tuberculosis (TB), caused by *Mycobacterium tuberculosis* (*M. tb*), has plagued humans for thousands of years and remains a major public health problem. Estimated by the World Health Organization (WHO), there were 10 million TB cases and 1.6 million TB deaths worldwide in 2017 [1]. Among them, 890,000 new TB cases (8.9%) were infected in China, with a mortality rate of 26/100,000 [1]. TB is a curable disease, and the modern TB control program recommends the strategy of directly observed treatment – short-course therapy, which is a six-month standardized treatment using first-line anti-TB drugs (FLDs) including Isoniazid (INH), Rifampicin (RFP), Pyrazinamide (PZA), and Ethambutol (EMB). This potent standardized drug regimen has contributed to an up to 90% cure rate in TB patients during the last three decades. However, the high rate of recurrence and retreatment among TB patients, the ubiquity of severe gastrointestinal adverse reactions [1, 2], and the increasing epidemic of multidrug-resistant tuberculosis (MDR-TB) all suggest that the effectiveness of anti-TB treatment in China has yet to be addressed.

Therefore, introducing new knowledge and clinical strategies to improve the therapeutic effect and clinical prognostics in Chinese TB patients is of great significance. The recent research advances in gut microbiome have shown that these bacteria are not only actively involved in the absorption of food and drugs but also produce bioactive compounds influencing the immune and hormone systems, which is essential to maintain vital functions of the healthy host [3]. Generally, the human gut microbiota shows a large degree of interpersonal diversity [4], and its composition is also affected by many factors such as geography, diet, season, lifestyle, disease state, and in particular, the use of antibiotics [3, 5].

Mounting evidence has shown that antibiotics administration could result in the dysbiosis of gut microbiota which was associated with many clinical concerns including accumulation of resistance genes [6], increased susceptibility to pathogens [7, 8], and compromised immune homeostasis and tolerance [9]. Different antimicrobial agents can influence the gut microbiota in different ways. The widespread use of the FLDs using a mixture of broad-spectrum (RFP) and mycobacterial specific antibiotics (INH, PZA, EMB) for at least 6 months is a long-term, combined, and large dose antibiotic therapy. RFP has a broad-spectrum activity against a wide range of Gram-positive and Gram-negative bacteria [6]. Even for narrow-spectrum antibiotics, drugs might affect other microbes in the body, either directly by their antimicrobial activity or by host immune system modulation [10]. Referred to previous population-based studies, 20 to 25% of TB patients suffered from gastrointestinal adverse reactions and liver dysfunction during anti-TB treatment [11], which directly damaged the intestinal mucosa and led to the reduced drug absorption and liver metabolism [12].

Recent studies carried out in TB patients indicated that standardized first-line anti-TB treatment caused acute changes in the intestinal microbiota, although information on diversity changes and the altered taxa are limited. Very few studies had taken a prospective approach and most of these studies had a cross-sectional design with small sample sizes and potential heterogeneity in study participants [13–15]. Additionally, the aforementioned evidence only clarified the acute microbiome changes within the first 2 months of anti-TB treatment. As a therapy with at least 6 months of antibiotics administration, it is of great importance to systematically investigate the long-term effect of anti-TB treatment on patients’ gut microbiota and the potential influence of gut microbiota alterations on treatment outcomes and drug-induced adverse effects. Therefore, a well-controlled prospective study is needed to provide a better understanding of these questions.

## Methods/design

### Objectives

#### Primary objective

The primary objective of this study is to explore the effects of continuous administration of FLDs on the gut microbiota by analyzing its alterations on diversity and taxonomic composition in pulmonary TB patients in China.

#### Secondary objectives

To describe the baseline features of gut microbiota before anti-TB treatment among TB patients with different age, gender, health status, disease comorbidity in different regions of China.To compare the characteristics of gut microbiota in terms of diversity and taxonomic composition between TB patients at baseline and healthy controls.To describe the incidence of gut microbiota dysbiosis during anti-TB treatment and its association with adverse effects and unfavorable treatment outcomes in pulmonary TB patients through a case-control study nested in the conducted cohort.To identify the potential microbial markers of unfavorable treatment outcomes.To observe the long-term effect of TB treatment on intestinal microbiota after therapy is completed.

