### Study design

This study is an ongoing multicenter, population-based prospective cohort study conducted in three TB designated hospitals in Eastern and Western China. The study aims to include 300–400 bacteriologically confirmed pulmonary TB patients. Baseline information, including demographics, socioeconomic status, laboratory tests, and disease profiles, as well as sputum and stool samples will be collected from the enrolled patients immediately after TB diagnosis. The patient cohort will be built and followed up during the first-line anti-TB treatment at Day-14, Month-2, Month-5, last day of treatment, and the sixth month after treatment. Information regarding adverse effects, disease progress, and laboratory results will be collected at each visit. Stool samples will be sent to the laboratory for 16S ribosomal ribonucleic acid (rRNA) gene sequencing to identify the alterations in gut microbiota. A comparison of gut microbiota will be performed between newly diagnosed TB patients and healthy controls to reflect the difference in baseline features. After treatment completion, a nested case-control study will be performed between patients with treatment success or failure and patients with or without adverse effects to screen the potential biomarkers from the gut microbiota indicative of therapeutic effect.

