### Sample size

Because of the absence of prior data on the study aims of the microbiota in a cohort study design of this topic, a pragmatic approach is chosen to determine the sample size. Based on the previous collaboration with the study sites, each site should enroll 50 eligible TB patients every year so that a patient cohort of 300 cases is expected within 2 years. Referred to the treatment failure rate (10%) in China [1], 30 patients in the conducted cohort are estimated to have unfavorable treatment outcomes. The sample size of microbiota study is usually selected empirically, a wide range of study settings indicates that 30 patients each group would likely be sufficient to assess phenotypic heterogeneity at the molecular level [21, 22].

Healthy controls will be equally recruited from the population taking routine health check-up in Sichuan and Shanghai with a total amount of 60. By assuming the rates of intestinal flora dysbiosis are 20% in TB patients [11] and 5% [23] in healthy controls [23], the sample size of 200 TB patients and 60 healthy controls has over 85% power to detect a significant difference in the composition of gut microbiota at the 5% significance level.

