### Study procedures

Patients with bacteriologically-confirmed TB are informed about the study by the study coordinators. After receiving the written informed consent, socio-demographic characteristics (date of birth, gender, education, income, etc.), behaviors (alcohol use, smoking, etc.) and clinical information (concomitant medication, physical examination results, TB severity, etc.) of the participants will be documented by a well-designed structured questionnaire.

According to the national guidelines of TB treatment in China, all drug-susceptible TB patients are recommended hospitalization (2 weeks) for the start of TB treatment. The standardized first-line treatment regimen is comprised of 2 months intensive phase and 4–6 months continuation phase. Considering different treatment stages and national regulations, enrolled TB patients will be sampled at Day-0 (important to sample BEFORE treatment), Day-14, the end of intensive-phase (usually at Month-2), Month-5, the end of the treatment and the sixth month after completion of therapy. During treatment, the disease progresses, adverse effects, TB-scores [24], clinical manifestations, drug regimen, and doses of the patients will be documented. Smear microscopy testing is performed at Day-0, Month-2, Month-5 and the end of therapy. DST testing is carried out at inclusion. Additionally, in total six fecal samples will be collected from the patients at inclusion and each scheduled follow-up visit. Subjects in the healthy control arm will have their fecal specimens collected once at inclusion. Questionnaires will be used to record the socio-demographic and behavioral information as well as the health check-up results.

The bio-specimen will be transported to the TB laboratory at the designated hospitals or local Centers for Disease Prevention and Control within 12 h after collection. Stool samples should be stored at − 80 °C until DNA extraction. Figure 1 and Table 2 provide an overview of the study flow-chart and the timeline of sample and information collection.

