#### 16S rRNA gene sequencing

Collected fecal samples will be analyzed by 16S rRNA gene sequencing to obtain the information on microbial composition. A nested polymerase chain reaction (PCR) protocol will be employed to amplify and barcode the 16S hypervariable region V3–V4 (primers: 314F: 5′-CCTACGGGRSGCAGCAG-3′ and 806R: 5′-GGACTACVVGGGTATCTAATC-3′) producing ∼425 base pair PCR product. PCR amplification will be performed in 20 μL reactions containing 10× polymerase mix (Life Technologies, Carlsbad, CA, USA), 10 μM of the forward and reverse primers, and 25 ng of template DNA. The PCR program is set as: initial denaturation at 95 °C for 5 min; 25 cycles of denaturation at 95 °C for 30 s, annealing at 56 °C for 30 s, and extension at 72 °C for 40 s; and final extension of 72 °C for 10 min. The dual-indexed amplicon mixture will be pooled according to the manufacturer’s instructions (Illumina, Inc., San Diego, CA, USA), and then sequenced on the Illumina HiSeq 2500 platform to produce 2 × 250 base pair reads.

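### The outcome and adverse-effect associations are labelled a nested case-control study with 30 per group called sufficient, although the whole cohort is to be sequenced; sampling controls would save no assay cost and could only lose precision

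*Protocol article*

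**What the plan says.** **Design.** The Secondary objectives combine two aims in one sentence: the incidence of dysbiosis during treatment, and its association with "adverse effects and unfavorable treatment outcomes in pulmonary TB patients through a case-control study nested in the conducted cohort". Study design states that, once treatment is complete, "a nested case-control study will be performed between patients with treatment success or failure and patients with or without adverse effects". The Methods paragraph of the Abstract describes the same comparison without the case-control label: diversity and composition "will be compared between the groups with and without unfavorable treatment outcome in terms of adverse effect and treatment failure".

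**Size.** Sample size expects that "each site should enroll 50 eligible TB patients every year so that a patient cohort of 300 cases is expected within 2 years". It continues: "Referred to the treatment failure rate (10%) in China [1], 30 patients in the conducted cohort are estimated to have unfavorable treatment outcomes". It then remarks that "30 patients each group would likely be sufficient to assess phenotypic heterogeneity at the molecular level". The article gives no control-to-case ratio, matching rule or sampling fraction. Study design gives a slightly wider enrolment target of 300–400.

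**Sequencing.** Study procedures state that "in total six fecal samples will be collected from the patients at inclusion and each scheduled follow-up visit". The sequencing section says: "Collected fecal samples will be analyzed by 16S rRNA gene sequencing to obtain the information on microbial composition". Neither names a subset, and the primary objective (the effect of first-line drugs on diversity and composition) needs these data from the cohort.

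**The concern.** A nested case-control design is chosen when the exposure is too costly to measure in everyone. Cases are then measured in full and controls are sampled. Here the exposure is the microbiota profile, and the primary objective already requires it for the cohort. The usual reason for sampling controls is therefore absent, and the article gives no other.

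The label still matters because cases are scarce. The number of failures cannot be raised by design, so the only free source of precision is the non-case group. An analyst who follows the label together with the remark about 30 in each group could compare 30 with 30 and leave 240 of the 270 non-cases with sequenced samples out of the analysis. The link between microbiota and treatment outcome is part of the study's stated aim, so a plan that permits this should be corrected.

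The same sentence also asks for the incidence of dysbiosis. A sample selected on outcome does not give that directly; the cohort does.

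**Working it through.** **Inputs from the article**
- Cohort: 3 sites × 50 per year × 2 years = 300 (Sample size).
- Failure rate 10% (Sample size).
- Gastrointestinal adverse reactions and liver dysfunction: 20 to 25% (Background).
- Wilcoxon test for two-group comparisons, significance at 0.05 (Microbiome analysis).

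**Assumptions, not in the article**
- Two-sided testing.
- A difference of 0.5 SD in a continuous microbiota measure, with 0.4 and 0.6 SD as a range.
- Wilcoxon efficiency of 0.955 relative to the t-test.
- No adjustment for multiple testing, dropout or repeated measures.

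**Step 1: the plan's own figure.** 300 × 0.10 = 30 cases, leaving 270 non-cases. The stated 30 is reproduced.

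**Step 2: standard error.** In SD units, SE = √[(1/n₁ + 1/n₂)/0.955].
- 30 vs 30: √(0.06667/0.955) = 0.264
- 30 vs 60: √(0.05000/0.955) = 0.229
- 30 vs 120: √(0.04167/0.955) = 0.209
- 30 vs 270: √(0.03704/0.955) = 0.197

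**Step 3: power and detectable difference.** Power = Φ(d/SE − 1.96). The difference detectable with 80% power is (1.96 + 0.8416) × SE. Relative efficiency is (1/30 + 1/270)/(1/30 + 1/n₂).

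| Controls used | Power, 0.4 SD | Power, 0.5 SD | Power, 0.6 SD | Detectable at 80% | Efficiency against all non-cases |
|---|---|---|---|---|---|
| 30 (1:1) | 33% | 47% | 62% | 0.74 SD | 56% |
| 60 (1:2) | 42% | 59% | 75% | 0.64 SD | 74% |
| 120 (1:4) | 48% | 67% | 82% | 0.59 SD | 89% |
| 270 (all) | 53% | 72% | 86% | 0.55 SD | 100% |

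Without the 0.955 factor, the 0.5 SD column runs from 49% at 1:1 to 74% with all non-cases, so the pattern does not depend on the test. For a binary dysbiosis marker at an assumed 40% in cases and 20% in non-cases, power is 39% for 30 vs 30 and 68% for 30 vs 270.

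**Step 4: adverse effects.** 300 × 0.20 = 60 and 300 × 0.25 = 75 cases, so a figure of 30 per group does not describe this comparison. With the Step 3 formula, the detectable difference is:
- 60 cases: 0.52 SD (60 vs 60), 0.41 SD (60 vs 240)
- 75 cases: 0.47 SD (75 vs 75), 0.38 SD (75 vs 225)

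**Step 5: how firm the 30 failures are.** If exactly 10% fail, the binomial chance of at least 30 failures is 53% with 300 evaluable patients. With an assumed 15% loss (255 evaluable, 25.5 expected) it is 20%. At the upper enrolment target it is 96% with 400 evaluable and 79% with 340, the latter being 400 less the same assumed 15%.

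**The case against.** The strongest objection is that the article never says that controls are sampled one to one or that non-cases are dropped. A reader might infer from the case-control label and the 30-per-group remark that about 240 patients will be discarded. The text does not support that as a statement of the plan. The 30 is an expected case count, followed by a remark on what is generally sufficient. The Abstract and Study design can both be read as comparing all patients with the outcome against all without it, and on that reading the loss is nil. Control selection is also a detail that a condensed article may leave to the full protocol. All of this stands, and it makes the loss conditional.

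Other stronger readings also fail:
- **Adjustment.** Sampling controls would not prevent covariate adjustment. The case count is the main limit, and Microbiome analysis already plans models with confounders.
- **Follow-up.** Attrition up to the visit six months after treatment does not determine the failure count. Table 2 records treatment outcome at the end of therapy, after a course that the Discussion puts at 6–8 months.
- **Incidence.** The sentence can be read as attaching the case-control study to the association only, with incidence taken from the cohort.

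What remains does not depend on missing detail. The article names a design twice, supports it with a per-group figure, and has the collected samples sequenced. If controls are sampled, the sampling saves no assay cost. If they are not, the design is misnamed.

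**Conclusion.** The point holds in conditional form. The nested case-control label has no stated rationale when the cohort is sequenced anyway, and the 30-per-group remark invites an inefficient comparison without fixing one. For 30 failures and an assumed 0.5 SD, the cost ranges from 25 percentage points of power at 1:1 (47% against 72%), through 13 at 1:2 and 5 at 1:4 (67% against 72%), to none if all non-cases are used. The effect size is an assumption because the article gives none for this comparison. The case count assumes 300 evaluable patients and a 10% failure rate. Discarding most non-cases is not an established feature of the plan. The text should be corrected on either reading, because the better analysis costs nothing.

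**What to change.** - **Secondary objectives and Study design:** replace the nested case-control study by a full-cohort comparison of all evaluable patients, analysed separately for treatment failure and for adverse effects. Use logistic or penalized logistic regression with a short covariate list suited to about 30 failures, for example site, age, sex and TB severity. If there is a reason to sample controls, state it together with the ratio and the selection rule.
- **Dysbiosis incidence:** state that it is estimated in the whole cohort.
- **Sample size:** replace the 30-per-group remark by the expected failures (about 30 of 300, fewer with loss) against all other evaluable patients, and about 60–75 patients with adverse effects against the rest. Give the detectable differences (about 0.55 SD for failure and 0.38–0.41 SD for adverse effects before any loss), and label the effect size and any loss rate as assumptions.

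The cost is a change of wording and analysis plan. No further samples, sequencing or data collection are needed.

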### Study design

This study is an ongoing multicenter, population-based prospective cohort study conducted in three TB designated hospitals in Eastern and Western China. The study aims to include 300–400 bacteriologically confirmed pulmonary TB patients. Baseline information, including demographics, socioeconomic status, laboratory tests, and disease profiles, as well as sputum and stool samples will be collected from the enrolled patients immediately after TB diagnosis. The patient cohort will be built and followed up during the first-line anti-TB treatment at Day-14, Month-2, Month-5, last day of treatment, and the sixth month after treatment. Information regarding adverse effects, disease progress, and laboratory results will be collected at each visit. Stool samples will be sent to the laboratory for 16S ribosomal ribonucleic acid (rRNA) gene sequencing to identify the alterations in gut microbiota. A comparison of gut microbiota will be performed between newly diagnosed TB patients and healthy controls to reflect the difference in baseline features. After treatment completion, a nested case-control study will be performed between patients with treatment success or failure and patients with or without adverse effects to screen the potential biomarkers from the gut microbiota indicative of therapeutic effect.

### Settings

Considering the differences in dietary habits, local economy and TB epidemic, patient recruitment for this study will take place at three geographic locations, i.e. Sichuan province, Jiangsu province, and Shanghai.

Shanghai (30°N 120°E) is an international metropolitan city in China with an estimated 24 million residents [16], first-ranked per capital disposable income and lowest TB report rate (14.75/100,000) in 2017 (Table 1) [17]. As one of the richest provinces in China, Jiangsu is located on the eastern coast of China next to Shanghai with the middle level of TB epidemic (33.52/100,000 [18]). On the contrary, Sichuan is an inland province located in Western China. Compared to the other two study sites, the income level, sanitation condition and health resources in Sichuan are less developed [16]. The notification rate of TB in Sichuan was 69.41 per 100,000 in 2017 [19], higher than the average level in China [20]. Regarding the dietary habits, Sichuan is famous for spicy food and high salt intake while people in Shanghai and Jiangsu prefer the light and sweet taste.

**Table 1 Tab1:** Economy, health resources and tuberculosis epidemic in study sites in 2017

Study sites	Per capita GDP^a^($)	Per capita disposable income ($)	Medical technical personnel in health care institutions (per 1000 persons)	Notified TB^b^ incidence rate (per 100,000 persons)
Sichuan	6671	2980.12	6.39	69.41
Jiangsu	16,010	5071.75	6.82	33.52
Shanghai	18,931	8541.93	7.73	14.75

^a^*GDP* Gross domestic product, ^b^*TB* Tuberculosis

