**Fig. 1 Fig1:**
[figure not shown]
Flow-chart of participants enrollment and follow up. Note: TB, tuberculosis; MDR-TB, multidrug-resistant tuberculosis

**Table 2 Tab2:** Summary of data collection and timeline

Timeline	Day-0	Day-14	Month-2	Month-5	End of therapy	6th month after treatment
Demographics						
Age, Sex, Occupation	X					
Financial situation	X					
Health conditions						
Comorbidities	X					
Smoking status	X					
Drinking status	X					
Clinical variables						
TB diagnostic information^a^	X					
Physical examination	X	X	X	X	X	X
Renal and liver function tests	X	X	X	X	X	X
Erythrocyte Sedimentation Rata testing	X	X	X	X	X	X
Sputum smear test	X	X	X	X	X	
TB-Score	X	X	X	X	X	
Chest X-ray	X		X	X	X	
Drug susceptibility test	X					
Current medication	X	X	X	X	X	
Drug dose	X	X	X	X	X	
Adverse effect		X	X	X	X	X
Treatment outcome					X	
Biological specimen collection						
Stool sampling	X	X	X	X	X	X
Sputum sampling	X		X	X	X	

^a^*TB* Tuberculosis

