#### Microbiome analysis

The raw 16S rRNA gene data will be processed to generate amplicon sequence variants (ASVs) using DADA2 program [25]. Taxonomies will be assigned using Silva [26] as the reference database. Alpha diversity (such as Observed ASVs, Chao1, Shannon, Simpson, etc.) and beta diversity measures will be analyzed using QIIME2 [27] and the Wilcoxon and Kruskal–Wallis tests will be used for statistical testing of two and multi-group comparisons, respectively. Principal coordinate analysis will be used to interrogate the robustness of group-wise clustering, and Adonis test will be used to estimate statistical significance of group-wise beta diversity [27]. Generalized linear model (GLM) will be performed to evaluate the influence factors that may affect the gut microbiota of patients, such as gender, body mass index, TB severity, age, morbidities and so on [28]. Then using GLM to estimate the dynamic changes of microbiota composition with the control of selected confounders [29]. Differential abundance analysis of ASVs will be carried out using STAMP [30] and *p*-values will be adjusted for multiple testing (FDR-adjusted Wald Test). Correlations between clinical parameters and bacterial genera will be calculated using canonical correspondence analysis or redundancy analysis [31]. Random forests approach will be performed to find the most important species as marker taxa correlating with unfavorable treatment outcomes. The data will be analyzed using the QIIME2 pipeline and R [32]. A *p*-value or q-value ≤0.05 will be considered as statistically significant.

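### The Day-14 change cannot separate the first-line drugs from the required hospital stay, and patients from three sites are compared with controls from two with no site term stated

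*Protocol article*

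**What the plan says.** **Site and diet.** Background says of the gut microbiota that "its composition is also affected by many factors such as geography, diet, season, lifestyle, disease state". Settings then gives diet as one reason for the choice of sites ("Considering the differences in dietary habits, local economy and TB epidemic, patient recruitment for this study will take place at three geographic locations") and describes the contrast: "Sichuan is famous for spicy food and high salt intake while people in Shanghai and Jiangsu prefer the light and sweet taste".

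**Hospital stay.** The patient inclusion criteria require willingness to be treated in hospital for the first two weeks. Study procedures places that stay at treatment start: "all drug-susceptible TB patients are recommended hospitalization (2 weeks) for the start of TB treatment". Stool is sampled before treatment, at Day-14, Month-2, Month-5, the end of treatment and six months later. Controls give one sample, at inclusion.

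**Controls.** Sample size plans 60 controls, split equally between Sichuan and Shanghai. Patients come from all three sites, at 50 per site per year for two years.

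**Data items.** Table 2 ("Summary of data collection and timeline") has rows for finances, smoking and "Drinking status" at Day-0, but no diet row at any visit. Study procedures describes the questionnaire with an open list, "behaviors (alcohol use, smoking, etc", and does not name diet.

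**Analysis.** Microbiome analysis states Wilcoxon and Kruskal–Wallis tests for group comparisons, an Adonis test for beta diversity, and a generalized linear model (GLM) whose factors are given as "such as gender, body mass index, TB severity, age, morbidities and so on". A second GLM describes change over time, with confounders still to be selected. Site, diet and hospital stay are not named. Region appears only in the first secondary objective, which describes baseline features.

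**The concern.** The primary objective attributes changes in the microbiota to the FLDs. At Day-14, each patient has started the drugs and spent two weeks in hospital, probably with different food and surroundings. The stay is common to all patients and nobody is followed without treatment, so no covariate can separate the two. Read as written, the plan would credit the whole Day-14 change to the drugs.

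The second problem concerns differences between patients, not changes within them. If site affects the microbiota, as the article expects, two groups with different site mixes will differ even when TB status or outcome has no effect. This applies by design to patients versus controls. It may also arise between outcome or adverse-effect groups if those events are unevenly spread over the sites.

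**Working it through.** **1. Which contrasts contain the hospital stay**

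| Contrast from Day-0 | Required stay | Untreated comparison over time |
|---|---|---|
| Day-14 | fills the whole interval | none |
| Month-2 | over for roughly six weeks | none |
| Month-5, end of treatment, six months later | over | none |

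The mixing is therefore mainly a Day-14 problem. Month-2 is already scheduled and lies outside the required stay.

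**2. Scale of the Day-14 problem (illustration only)**

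The documents give no hospital effect. Assume that the stay alone shifts a diversity index by 0.1 to 0.3 SD, that the change has an SD of 1 on the same scale, and that all 300 pairs are complete. The change has SD √(2(1 − ρ)), so an SD of 1 implies a within-patient correlation ρ of 0.5.

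- SE = 1/√300 = 0.058 SD
- 0.1/0.058 = 1.7 SE; 0.3/0.058 = 5.2 SE

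This shows only that, at this sample size, a small shift could pass for a significant drug effect.

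**3. The plan's own power figure**

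Inputs from Sample size: dysbiosis 20% in 200 patients, 5% in 60 controls, 5% level (two-sided assumed). The pooled-variance two-proportion formula gives 85.8%, which agrees with the stated figure of over 85%. This point does not dispute that figure.

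**4. Site mix in the patient–control comparison**

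Let S, J and H be the levels in Sichuan, Jiangsu and Shanghai, with no effect of TB. Patients are spread 1/3 per site (50 × 2 = 100 each, 300 in total), and controls are 1/2 Sichuan and 1/2 Shanghai.

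Spurious difference = (S + J + H)/3 − (S + H)/2 = (2J − S − H)/6

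| Assumed S / J / H | Spurious difference |
|---|---|
| 10% / 20% / 10% | (40 − 10 − 10)/6 = +3.3 points |
| 30% / 10% / 10% | (20 − 30 − 10)/6 = −3.3 points |

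The planned difference is 20 − 5 = 15 points. If only Sichuan and Shanghai patients are used, in equal numbers, the spurious difference is (S + H)/2 − (S + H)/2 = 0. Those two sites are expected to give 2 × 100 = 200 patients, the number in the power statement, but the text does not say that the comparison is so limited.

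**5. Cost of that limit**

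On the plan's own rates, power is 89.0% for 300 versus 60 and 85.8% for 200 versus 60, a loss of 3.2 points that still leaves the stated target met.

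**6. Within-patient change**

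A stable site or diet effect enters both of a patient's samples and cancels in their difference. This protection is lost if visits are compared as independent groups, which is how a Kruskal–Wallis test treats them.

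**The case against.** The case on the other side is substantial, and much of it stands.

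- **A reader might infer that diet was not collected.** The documents do not show this. The questionnaire is not shown, its description is open-ended, and Table 2 is a summary that also omits education, which Study procedures does record. What can be said is that no listed item records diet.
- **A reader might infer that site is ignored or cannot be recovered.** Region is in a secondary objective, the list of GLM factors is open, and site is known for every patient. Adjustment needs no new data. It remains true that the group-wise tests are stated without site while controls come from two of the three sites.
- **A reader might infer that regional diet distorts the primary longitudinal result.** With paired analysis, stable differences cancel. Adding site or usual diet to a model would not cure Day-14 either, because the stay does not vary between patients.
- **Day-14 is one of five post-baseline visits.** Nothing makes it the primary contrast, and the article stresses long-term effects. In addition, Day-0 is defined as before treatment, not before admission, so a change of surroundings between the two samples is likely but not stated. This limits the reach of the point. It does not make the Day-14 change attributable to the drugs alone.
- **Adjusting for on-treatment diet or appetite could do harm.** Background reports gastrointestinal reactions and liver dysfunction in 20 to 25% of patients on treatment, so appetite may be a consequence of the drugs. Adjusting for it could remove part of the effect under study. This stands and shapes the fix.

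**Conclusion.** The point holds in a limited form. By design, the Day-0 to Day-14 change is the joint effect of FLDs and hospital stay, and the article does not say so. Between-patient comparisons, above all patients versus controls, are open to a site effect that the stated tests do not remove.

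Neither size is known. The range of 1.7 to 5.2 standard errors rests wholly on an assumed shift, and it would be wrong to read it as a known bias. The 3.3 points rest on assumed site levels and on using all 300 patients unadjusted; with equal numbers from Sichuan and Shanghai only, this site-mix bias is zero. The later visits, the stated power and paired within-patient changes are not put in doubt. The change is worth making because the main corrections use data already in hand.

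**What to change.** 1. **Day-14.** Report the Day-0 to Day-14 change as the combined effect of FLDs and hospital stay. Rest the early drug claim on the scheduled Day-0 to Month-2 contrast, noting that this is still a before–after comparison without an untreated group. Cost: wording.
2. **Between-patient comparisons.** For patients versus controls, outcome groups and adverse-effect groups, include site in the GLM and restrict Adonis permutations within site. Limit the patient–control comparison to Sichuan and Shanghai, which reduces the expected patient group from 300 to 200. Site terms also cost some precision in the outcome analysis: about 30 failures over three sites is about 10 per site if evenly spread.
3. **Visit comparisons.** State that they are paired within patient. Cost: wording.
4. **Diet.** State whether the questionnaire records it. If not, add a brief item. Adjust only for baseline, pre-treatment diet, and use on-treatment diet or appetite descriptively or in a sensitivity analysis. This takes a few minutes per visit, and diet will be missing for patients already enrolled since recruitment opened in July 2018.
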